## Methods/design

### Trial design

The Walk 2.0 project is a three-arm randomised controlled trial (RCT) investigating the effectiveness of two web-based PA interventions and a logbook PA intervention (Figure 1). Outcomes will be assessed at baseline, and at 3, 12, and 18 months. The study has received ethics approval from the Human Research Ethics Committees of the University of Western Sydney (Reference number H8767) and CQUniversity (H11/01-005). The study will be reported according to CONSORT guidelines [32].

**Figure 1 F1:**
[figure not shown]
Flow diagram of study protocol.

### Participants and recruitment

A total of 504 participants will be recruited for this study across two sites in Australia (South Western Sydney and Central Queensland). The primary means of recruiting participants will be a personalised invitation letter to an extract of randomly selected individuals from the Australian Electoral Commission (AEC) electoral roll. Voting is compulsory for persons aged 18 years and over in Australia and AEC data provides an effective means of sampling the targeted population. Previous research utilising a similar method to recruit participants, but requiring mainly survey-based cohort measurements, reported that between 60 and 70% of individuals invited to a research project using this manner, participated [28,29]. The participant requirements of this research, however, are higher than these other studies, and, thus a response rate of less than 10% is anticipated. Therefore, an extract of 14,000 names and addresses - 7,000 from each of the Federal electoral divisions of Capricornia (Rockhampton, QLD) and Werriwa (South Western Sydney, NSW) - matched by age and gender, was obtained from the AEC electoral roll. A number of other recruitment methods will also be utilised to supplement the primary recruitment method and to recruit a diverse range of participants. These methods include advertising in local print media, calling former research participants who had registered their interest in participating in future research, and messages delivered through university email lists.

### Eligibility

To be eligible for the study, individuals must live or work in South Western Sydney (New South Wales) or Rockhampton (Queensland), be willing to increase the amount of physical activity that they are currently taking part in, and be over 18 years of age. Participants will be excluded from the project if:

1. They do not have access to the Internet.

2. Are unable to speak/read English.

3. They are currently engaging in moderate-to-vigorous PA (MVPA) for 30 minutes on 5 or more days per week, with the question “As a rule, do you do at least half an hour of moderate or vigorous exercise (such as walking or a sport) on five or more days a week?” [33].

4. They have an existing medical condition which could be exacerbated by PA (assessed using the Physical Activity Readiness Questionnaire, PAR-Q [34]).

5. They have ever been a member of http://www.10000steps.org.au.

Subsequent to the commencement of recruitment, additional screening for participants who self-identified as being either too physically active to participate in the study or as having an existing chronic medical condition (based on the PAR-Q measure) was introduced and will be conducted by telephone interview. The Active Australia questionnaire will be used to address potential recall bias by confirming the participant’s assessment of PA [35,36]. Individuals who self-identify as having an existing chronic medical condition will be invited to gain medical clearance from their general medical practitioner (family physician) to participate in the study, as some people are likely to still benefit from participating in the study given suitable medical clearance (e.g., those taking prescribed blood pressure medications).

### Study procedure

Participant eligibility will be screened through a self-administered survey that is delivered with a personalised invitation letter (AEC-recruited participants) and a reply-paid envelope. Online access to the screening survey will also be available for all potential participants. As indicated above, additional screening concerning PA and health status may be needed for some people. All those deemed eligible will then be contacted by telephone and invited to attend an induction session to provide informed consent and be fitted with an ActiGraph activity monitor to measure PA, which they are required to wear for 7 days. Participants will be asked to complete a log of wear time, showing time that the monitor was put on and taken off each day and the time and reason that the monitor was taken off during the day. When participants return the ActiGraph (at least 8 days later) they will participate in the baseline measurement session. All measurements sessions (baseline, 3, 12 and 18 months) will incorporate anthropometic measures and a self report questionnaire (Table 1) and will be conducted at a University campus. ActiGraph monitors will be posted to participants by registered post for 3, 12 and 18 month follow ups a week before they attend their measurement session at the university. Participants will be randomly allocated to an intervention condition and all participants will receive a pedometer (Yamax Digiwalker SW200, Yamasa Tokei Keiki co., Japan) after satisfactorily completing the requirements of the baseline measurement (valid Actigraph data, completed anthropometric assessments, completed baseline survey). Participants’ progress and use of the website will not be monitored between follow-up measurement points.

**Table 1 T1:** Summary of measures to be collected

**Primary outcome measures**	**Data collection instrument**	**Collection points (months)**
Physical activity levels	7 day ActiGraph physical activity monitoring	0, 3, 12 and 18
	Active Australia Survey [35]	0, 3, 12 and 18
**Secondary outcome measures**		
Anthropometric measurements	Height	Induction, 0, 3, 12 and 18
	Weight	Induction, 0, 3, 12 and 18
	Abdomen girth [37]	Induction, 0, 3, 12 and 18
**Other measures**		
Self reported quality of life	SF-36 [38]	0, 3, 12 and 18
Psychosocial Correlates	Stages of Change [39]	0, 3, 12 and 18
	Intention [40]	
	Subjective Norm [40]	
	Perceived Behavioural Control [40]	
	Attitude [40]	
	Outcome expectations [41]	
	Self Efficacy [42]	
	Barriers Self Efficacy [42]	
Self reported Internet self-efficacy	Internet self-efficacy scale [43]	0, 3, 12 and 18
User satisfaction	System Usability Scale [44]	3, 12 and 18 months
Descriptive information	Demographics questionnaire	0

If valid Actigraph data are not collected at a time point, the participant will be asked to wear the ActiGraph activity monitor for a further 7 days until valid data have been collected. Anthropometric measurements will be collected at all time points. If participants miss an assessment point at 3 or 12 months, they will still be invited to attend the next subsequent follow-up assessment session.

### Interventions

#### Web 1.0 group

Participants in the Web 1.0 condition will gain access to the existing 10,000 Steps website (http://www.10000steps.org.au). The 10,000 Steps website is designed in conjunction with the use of a pedometer and offers a step log and individual self-monitoring features as well as numerous written (electronic) educational/informational materials [27]. These features allow the core functionality of recording steps and monitoring progress over time in a web-based environment. Communication between participants on this site is limited to a forum and a virtual walking buddy feature which enables a user to share their step log with another user. In order to request a walking buddy, users must know the email address of their potential walking buddy and invite them via email; alternatively users can post their email address on the public forum and ask to be invited as a walking buddy by interested individuals. There is no function on the 10,000 Steps website that allows users to search for other users.

#### Web 2.0 group

Participants in the Web 2.0 condition will have access to a newly developed website (Walk 2.0) featuring Web 2.0 features The Walk 2.0 website has been developed to replicate the core functionality of the 10,000 Steps website with additional Web 2.0 features. These additional features have been developed around blogs, Google Mash-ups, social networking, and other Web 2.0 architecture. The website, when used with a pedometer, allows core functionality of recording steps and monitoring progress over time in a web-based environment while facilitating contact between participants through ‘status updates’, streams, blogs, virtual walking groups, internal emails, and forum posts. Participants have their own home page, allowing them to access specific information about their progress and personalised features for the site, such as mapping their favourite walks using a Google ‘mashup’ tool, ‘friend’ other users, access their friend’s content (providing consent has been obtained), and invite outside friends and family, who will be able to use the website but not be involved in the trial, to join the site. Users also have a profile page which allows them to share selected information with their ‘friends’ on the site. Access to the Web 2.0 platform will be restricted to those in the Web 2.0 arm and other individuals that participants invite to join them on the site.

#### Control group

Participants in the Control condition will have access to a paper-based log book and will be directed not to register or use the publicly available 10,000 Steps website. The log book provides participants with an overview of the key messages available through the other interventions, such as instruction in goal setting and increasing opportunities for PA and health gain, and a means of recording steps and monitoring progress over time. Each log book covers a period of 3 months and participants will receive enough log books at each follow-up measurement point to sustain their involvement in the project until the following measurement.

### Randomisation

Participants will be randomly assigned to one of the three trial arms using equal groups random allocation performed through a computer-generated algorithm. To avoid contamination in cases where participants reside in the same household, the first participant will be randomly assigned to a trial arm and the other participants from that household will also be allocated to the same trial arm. Randomisation occurs after the participant has completed all baseline measurements. Participants will receive a standardised introduction to the features of the intervention that they have been assigned to, which will include the use of the pedometer, self-monitoring, and setting goals in all groups; and how to modify account settings and access important features such as progress graphs and charts, forums, and the use of social media for the web-based groups.

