During the induction session participants will be instructed on correct wear and fitting of the ActiGraph activity monitor. Participants will be asked to wear the unit over their right hip at the point of the anterior superior iliac spine, and fastened with the supplied elastic waist band. Participants will also be asked to complete an activity monitor log detailing times the monitor was removed and activities undertaken when the Actigraph was not worn. The Activity monitor will be worn for 7 full days during waking hours, except when swimming or bathing and participating in contact sports. Triaxial data are collected in 1 second epochs along with step counts and inclinometry. When participants attend their baseline appointment at least 8 days later, the activity monitor data will be inspected. For the purposes of this study, valid wear time will be determined as at least 600 minutes wear time per day on 5 days. Wear time will be evaluated using the criteria of 60 minutes of consecutive zero data and a 2 minute spike tolerance [50]. Participants with invalid data will be asked to wear the activity monitor for a further 7 days. If, for the baseline measurement, a participant refuses or if they agree but return invalid data up to three times, they will be excluded from the study but allowed to continue using the website. Participants with valid data will then complete a baseline survey before being randomised to their trial intervention.

For 3, 12 and 18 month outcome measurements, activity monitors and wear log sheets will be delivered to participants using registered post. Receipt of the activity monitor will be confirmed by telephone and participants will also be contacted by telephone 2–3 days prior to the appointment to check wear compliance and confirm the scheduled follow-up appointment. If the participant reports compliance with expected wear of the activity monitor they will then attend the University where wear time will be validated according to the protocol described at baseline. If the participant reports non-compliance with the expected wear of the activity monitor, the monitor will be left with them for a minimum of a further 5 days, during which time they will be expected to wear the monitor to comply with project requirements. If the participant chooses not to wear the ActiGraph again they will be asked to complete the outcome survey and will not be excluded from the project.

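### Household members who enter after the first has been randomised inherit an arm that can already be known, so their enrolment and baseline are not protected from the allocation

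*Protocol article*

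**What the plan says.** The Randomisation section gives the reason for a household rule, "To avoid contamination in cases where participants reside in the same household", and then the rule itself: "the first participant will be randomly assigned to a trial arm and the other participants from that household" are given that same arm. Only one draw is made per household, and it is tied to the first person.

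The safeguard on timing is worded for one person at a time: "Randomisation occurs after the participant has completed all baseline measurements". The Physical activity section repeats it: "Participants with valid data will then complete a baseline survey before being randomised to their trial intervention".

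Consent is also individual. Under Study procedure, eligible people are "invited to attend an induction session to provide informed consent and be fitted with an ActiGraph activity monitor to measure PA". The monitor is then worn for 7 days and returned at least 8 days later, when the baseline session takes place. A person can still leave during this stage: if "a participant refuses or if they agree but return invalid data up to three times, they will be excluded from the study".

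The arm is open once assigned: "Participants will receive a standardised introduction to the features of the intervention that they have been assigned to".

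**The concern.** Completing baseline before randomisation ensures that neither the participant nor the staff can let the allocation influence who enters or what is recorded at baseline. The safeguard works only if the arm is unknown until baseline is finished. For a later household member the arm is not drawn at all. It is copied from someone they live with, who has already been shown the intervention and may be using it.

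Two things are at stake for such a member. The first is selection. The choice to attend induction, to re-wear the monitor after invalid data or to drop out during baseline can differ between a household with a website and one with a log book. The second is measurement. The baseline ActiGraph week and survey may be completed while the housemate is already active in the intervention, so that baseline MVPA is no longer a pre-intervention value. Intention-to-treat analysis and multiple imputation, both named under Statistical analysis, repair neither.

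**Working it through.** The protocol states no figure for this point, so the check is first one of sequence and then one of scale.

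**Sequence.** Let day 0 be the day the first household member is randomised. From then on the arm of every other member is certain. Three cases follow from the text.

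| Position of the other member on day 0 | Enrolment decision | Baseline data |
|---|---|---|
| Baseline already complete | Protected | Protected |
| Consented, baseline unfinished | Consent protected; re-wear and withdrawal exposed | All or part exposed |
| Not yet consented | Exposed | Wholly exposed |

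The sentence placing randomisation after the participant's own baseline can be obeyed to the letter in all three rows, because the other member is never randomised. The article does not limit household members to the first row. Entry at different times is plausible: the section on participants and recruitment adds print advertising, calls to former research participants and university email lists to the electoral-roll letters.

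The arm can also alter the incentive to enrol and eligibility. Under Web 2.0 group, family may be invited onto the site as users outside the trial. Under Eligibility, anyone who has ever joined the 10,000 Steps site, which is the Web 1.0 intervention, is excluded. A housemate's reasons to enrol, and even their eligibility, can thus depend on the first member's arm. The direction cannot be predicted.

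**Scale.** Inputs:

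- 504 participants, 168 per arm; 120 per group before inflation for dropout, 80% power, alpha 0.05 (Statistical power and sample size).
- f, the share of participants who are later household members: not given; assumed to be 2% to 20%, about 10 to 101 of 504.
- s, the arm-related mean difference among those members in SD units: not given; assumed to be 0.2 to 0.5.

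Detectable difference implied by the sample size, for a two-sided comparison of two means:

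(1.960 + 0.842) × √(2/120) = 2.802 × 0.1291 = 0.36 SD.

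The protocol calls its target only small to moderate; 0.36 is back-calculated.

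Shift in a between-arm contrast = f × s:

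| f (people) | s = 0.2 SD | % of 0.36 | s = 0.5 SD | % of 0.36 |
|---|---|---|---|---|
| 2% (10) | 0.004 | 1.1 | 0.010 | 2.8 |
| 5% (25) | 0.010 | 2.8 | 0.025 | 6.9 |
| 10% (50) | 0.020 | 5.5 | 0.050 | 13.8 |
| 20% (101) | 0.040 | 11.1 | 0.100 | 27.6 |

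The same product serves both mechanisms. If s is a difference in who joins, f × s is the shift in the outcome contrast before any adjustment. If s is a distortion of baseline MVPA in one arm, f × s is the error in a change-from-baseline contrast. A baseline-adjusted contrast with slope b for baseline would carry b × f × s.

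**The case against.** The strongest reply is that the article does not say that household members enter at different times. Its wording also fits couples who pass through screening, induction and baseline together, in which case nothing goes wrong. A journal article may leave such operating details to the full protocol. This is fair as to how often the problem occurs. It does not remove the problem, because the article states the allocation rule itself, in sequential form, and attaches the baseline condition to the individual. The fault lies in a rule as written, not in an omitted detail.

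A second reply concerns motive. A housemate drawn to the Web 2.0 site can be invited as a non-trial user, and one who registers on the 10,000 Steps site becomes ineligible. Both facts weaken the simple story that people enrol to gain access to a website. They also show that entry can differ by arm, so this reply only partly succeeds.

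A third reply concerns size, and it stands. The main recruitment route is letters to randomly selected individuals with an expected response below 10%, which gives no reason to presume many co-resident participants. If joiners differ from others in a stable way, an analysis using baseline would remove part of the shift. That helps less where the baseline itself was recorded after the housemate had started.

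A reader might infer that concealment fails throughout the trial. The documents do not support this: first-randomised members, people with no co-resident participant, and members who finish baseline before the household is assigned are all protected.

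**Conclusion.** The point holds for one subgroup: household members whose consent or baseline is not complete when the first member is randomised. For them, allocation is not concealed under the stated rule. Baseline MVPA can depend on the arm, and so can enrolment where consent has not yet been given.

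The effect on a between-arm contrast is about 0.004 to 0.10 SD, or roughly 1% to 28% of the implied 0.36 SD. This range rests entirely on the assumed share (2% to 20%) and the assumed difference (0.2 to 0.5 SD), and neither has a source in the article. The low end is as admissible as the high end. A reader might take a share of 10% to 20% as the expected case, or 0.36 SD as the planned effect; the article states neither. The direction of any bias is unknown.

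The change is worth making because it is cheap and preserves the purpose of the household rule. The likely size alone would not compel it.

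**What to change.** In the Randomisation section, make the household the unit of assignment. Ask at screening whether anyone else in the home intends to take part. Assign the household once, after every consenting member has completed valid baseline measurements. State that anyone who joins after the household has been assigned is not counted in the randomised comparison.

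For households already enrolled, add a sensitivity analysis restricted to first-randomised members. Where dates of consent, baseline completion and household assignment are available, report how many members were still incomplete at assignment. That count replaces the assumed 2% to 20%.

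The cost is one screening question, the loss of a few late joiners, one extra analysis and a wait for the first member of a multi-person household. The wait is usually short, but it lengthens if a housemate has to repeat the 7-day wear.

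Household members still share an arm, so the protection against contamination is kept.

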### Outcome measurements

#### Physical activity

Physical activity will be evaluated using both subjective (Active Australia Survey) and objective (ActiGraph activity monitor) methods. The Active Australia Survey assesses both frequency and duration of walking for transport and recreation and MVPA [35]. The Active Australia Survey has established acceptable test-retest reliability and validity in the Australian adult population, and has been documented as a useful evaluative tool for detecting intervention related change in PA behaviours [36,45,46]. The ActiGraph activity monitor (ActiGraph GT3X, http://www.theActiGraph.com) will be used to objectively measure minutes of MVPA. The GT3X will be affixed to an elastic belt and worn on the waist. The validity and reliability of the GTX3 has been shown to be similar to the Actigraph GT1M devices in laboratory testing and for the measurement of everyday activities [47,48]. The reliability and validity of GT1M compared to other commercially available activity monitors has been previously established as [49].

During the induction session participants will be instructed on correct wear and fitting of the ActiGraph activity monitor. Participants will be asked to wear the unit over their right hip at the point of the anterior superior iliac spine, and fastened with the supplied elastic waist band. Participants will also be asked to complete an activity monitor log detailing times the monitor was removed and activities undertaken when the Actigraph was not worn. The Activity monitor will be worn for 7 full days during waking hours, except when swimming or bathing and participating in contact sports. Triaxial data are collected in 1 second epochs along with step counts and inclinometry. When participants attend their baseline appointment at least 8 days later, the activity monitor data will be inspected. For the purposes of this study, valid wear time will be determined as at least 600 minutes wear time per day on 5 days. Wear time will be evaluated using the criteria of 60 minutes of consecutive zero data and a 2 minute spike tolerance [50]. Participants with invalid data will be asked to wear the activity monitor for a further 7 days. If, for the baseline measurement, a participant refuses or if they agree but return invalid data up to three times, they will be excluded from the study but allowed to continue using the website. Participants with valid data will then complete a baseline survey before being randomised to their trial intervention.

For 3, 12 and 18 month outcome measurements, activity monitors and wear log sheets will be delivered to participants using registered post. Receipt of the activity monitor will be confirmed by telephone and participants will also be contacted by telephone 2–3 days prior to the appointment to check wear compliance and confirm the scheduled follow-up appointment. If the participant reports compliance with expected wear of the activity monitor they will then attend the University where wear time will be validated according to the protocol described at baseline. If the participant reports non-compliance with the expected wear of the activity monitor, the monitor will be left with them for a minimum of a further 5 days, during which time they will be expected to wear the monitor to comply with project requirements. If the participant chooses not to wear the ActiGraph again they will be asked to complete the outcome survey and will not be excluded from the project.

